
#### Secondary outcome assessments

Muscle strength test of the ankle

The isokinetic strength of the ankle muscles will be measured using an isokinetic dynamometer (IsoMed 2000). An isokinetic test will be conducted at angular velocities of 30°/s [21]. During the ankle plantar and dorsal flexor test, the participants will lay supine on the dynamometer seat with their lower limbs in full extension. The foot will be placed on the foot adapter connected to the head of a dynamometer with an ankle angle at 0° of plantar flexion (neutral position of the talocrural joint). Static gravitational correction will be applied to negate the influence of the gravity-effect torque on the test data. During the ankle invertor and evertor testing, the head of the dynamometer and the test seat are adjusted to 80° and 45°, respectively. The participants will be seated on the dynamometer seat with their shin positioned horizontally to the ground. Three trials will be performed for each direction on each foot. The mean of three trials will be used for the analysis.

## Proprioception test of ankle

Ankle proprioception data will be collected using the Sunny proprioception instrumentation [22]. The participants will sit on a chair with the testing leg placed on the platform during the test. The participants will be asked to wear eye masks and noise-canceling headphones to eliminate any visual and auditory stimuli from the test environment. The ankle will be passively moved at a velocity of 0.4°/s in plantar flexion, dorsal flexion, inversion, and eversion direction by the platform. Once the participant could detect the motion of the leg, they will be asked to press a stop button to stop the platform. The participants will be asked to confirm the direction of the motion in case they are guessing the movements. The angular movement of the platform will be recorded as the threshold for the detection of the ankle joint movement. Three trials will be performed for each direction on each foot. The mean of three trials will be used for the analysis.

## Dynamic leap and balance test (DLBT)

DLBT is a novel test that involves a dynamic task with serial changes in the base of a sport, such as walking and running, to assess balance [23]. The pattern of the DLBT will consist of 11 total targets (one central target and two peripheral targets along each of the five directions) as the medial half of the SEBT for each foot. The short and long targets will be placed at 100% and 150% of the distance based on the average normalized SEBT reach distances. Each leap will require the participant to leap with one leg and land on the other. The time that the participant leaps from the central target to the peripheral target and back to the central target in the order of 1–10 will be recorded. The faster the participants perform, the better their condition will enhance. They will be asked to stabilize for 2 s each time they returned to the central target before jumping to the peripheral target. The mean values of the three trials will be used for the analysis.

### Participant timeline {13}

The time schedule of enrolment, visits for participants, intervention, and assessments are shown in Fig. 3.

### Sample size {14}

The sample size is estimated on G* Power software (Germany) on the basis of a previous study [12], which reported that the CAIT score increased from 17.6 ± 2.1 cm to 28.4 ± 2.4 cm after 12 weeks of Tai Chi training. Under a significance level of 0.05, a statistical power of 0.80 in the two-tailed test, and a drop-out rate of 20% [24], the effect size and estimated required sample size of two groups are 0.57 [12] and 104, respectively.

### Recruitment {15}

Recruitment will be carried out at Shandong Sport University in Shandong, China. Leaflets, posters, and recruitment advertisements will be distributed on WeChat. All potential participants will be screened by the research assistant with professional qualification for participation based on the inclusion and exclusion criteria listed above. After being initially screened for inclusion and exclusion criteria, eligible volunteers who agree to participate will sign a written informed consent before the intervention. Through the informed consent, the purpose, procedures, potential risks, benefits, and confidentiality of the information will be explained in detail. The informed consent process will be performed by the main researchers (HT). On the consent form, participants have the right to withdraw at any time and will be asked if they agree to the use of their data should they choose to withdraw from the trial. They will also be asked for permission for the research team to share relevant data with people from the universities taking part in the research or from regulatory authorities where relevant. This trial does not involve collecting biological specimens for storage. During the trial, the participants will be informed to avoid participating in any other regular rehabilitation training and maintain their previous lifestyle. There is no anticipated harm and compensation for trial participation. All subjects will be instructed to complete a questionnaire about the basic personal information and the medical history. They are available from the corresponding author on request. The patients were initially recruited on September 22, 2021.

## Assignment of interventions: allocation

### Sequence generation {16a}

After the baseline assessment, the participants will be randomly assigned to the STCEP group and the control group at a ratio of 1:1. SPSS version 22.0 (IBM, NY, USA) will be used for random allocation. A randomization sequence will be created by an independent research assistant.

### Concealment mechanism {16b}

Randomization will be placed into sealed opaque envelopes by an independent research assistant who is blinded about the trial and released later. Each participant’s identity will be represented by a serial number. The letters “A” and “B” represent the groups assigned, such as “STCEP group” and “control group.”

### Implementation {16c}

A randomization sequence will be created by an independent research assistant (A). The investigator (YC) will take charge of the participant recruitment (informing them the trial procedures and obtaining their informed consent before inclusion in the study). Furthermore, the research assistant (B) will assign the participants to interventions.

## Assignment of interventions: blinding

### Who will be blinded {17a}

Outcome assessors, data managers, and statistical analysts will be blinded to group assignment and letter representation. In addition, participants will be asked not to discuss their experiences during training if they incidentally encounter other participants.

### Procedure for unblinding if needed {17b}

Unblinding is permissible only when a serious adverse event or emergency rescue occurs.

## Data collection and management

### Plans for assessment and collection of outcomes {18a}

Two principal assessors will conduct a comprehensive training in the measures and be responsible for data collection. Interrater reliability will be determined, and discrepancies will be resolved by consensus. The questionnaires and laboratory tests used in this study have been widely used in other studies. They are available from the corresponding author upon request. Primary and secondary outcomes will be measured at baseline, 4th, 8th, and 12th weeks of training.

### Plans to promote participant retention and complete follow-up {18b}

Participants have the right to withdraw at any time and will be asked if they agree to the use of their data should they choose to withdraw from the trial. They will also be asked for permission for the research team to share relevant data with people from the universities taking part in the research or from regulatory authorities where relevant.

### Data management {19}

Some outcome data will be collected via the paper materials (writing participant identity in serial number). Data integrity and validity will be verified and independently entered by a research staff, and a duplicate copy will be stored in a separate password-protected hard drive. All data will be unmodifiable once input and checked. All computers and electronic systems will be kept in laboratories. Entry into laboratories was controlled by restricting all unauthorized individuals. Only the statisticians will have access to the database to conduct final statistical analyses.

### Confidentiality {27}

The information collected will be used for research purposes and analyzed under the protection of personal privacy. All personal information will not be shared or released.

### Plans for collection, laboratory evaluation, and storage of biological specimens for genetic or molecular analysis in this trial/future use {33}

Not applicable. This trial does not involve collecting biological specimens for storage.

## Statistical methods

### Statistical methods for primary and secondary outcomes {20a}

Data will be analyzed with SPSS 20.0 (IBMS, NY, USA) and expressed as mean ± standard deviation. Two-way repeated ANOVA will be used to determine the main effects of groups, intervention time, and interaction on the measurements. If any significant main and interaction effects will be found, the Bonferroni method will be conducted for post hoc comparisons. The significant level will be set at 0.05.

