#### Inclusion criteria

The initial sprain must have occurred at least 12 months prior to study enrollment, associated with inflammatory symptoms (pain and swelling), and created at least one interrupted day of the desired physical activity.They experienced at least two episodes of giving way in the 6 months prior to study enrollment.Their CAIT score must be ≤24.

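### The repeated-measures ANOVA lets time and group main effects open post hoc testing and names no deciding test; a baseline-adjusted week-12 comparison would answer the question directly and usually with more power

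*Protocol article*

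**What the plan says.** The section on statistical methods for primary and secondary outcomes {20a} fixes the model: "Two-way repeated ANOVA will be used to determine the main effects of groups, intervention time, and interaction on the measurements". It then sets the route to follow-up comparisons: "If any significant main and interaction effects will be found, the Bonferroni method will be conducted for post hoc comparisons". The level is 0.05. None of the three F tests is singled out, no visit is named as decisive, and no baseline covariate is mentioned.

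The sections on outcomes {12} and on assessment {18a} give the visits: "Primary and secondary outcomes will be measured at baseline, 4th, 8th, and 12th weeks of training". Section {20a} does not say in words that baseline is one of the levels of time, but with four listed visits and no covariate that is the natural reading.

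The objective {7} is the effect of the Tai Chi programme, and the trial design {8} is a randomised parallel comparison. The sample size section {14} states that "the effect size and estimated required sample size of two groups are 0.57 [12] and 104, respectively".

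**The concern.** The trial's question is whether the arms differ because of treatment. The three planned tests bear on it very differently.

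- **Time main effect.** This is change averaged over both arms. Entry requires a low score ("Their CAIT score must be ≤24"), so some regression to the mean in CAIT is expected. Every test is repeated four times, and controls also receive exercise and education. Both arms may improve whatever Tai Chi does.
- **Group main effect.** If baseline is a level, this averages in a visit before randomisation, where the expected difference is zero.
- **Interaction.** This does test differential change, but it spreads over 3 degrees of freedom and does not say at which visit the arms differ.

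Because main effects can open the post hoc comparisons and no deciding test is named, a trial with no treatment effect could report significant F tests and within-arm changes that are easily misread as efficacy. A real week-12 difference, meanwhile, would be tested less directly than the data allow. This is a stated choice and not a detail left to an analysis plan: a plan that followed the text would inherit it.

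**Working it through.** **Inputs from the protocol.** Effect size 0.57 (type not stated; read here as a standardised mean difference), two-sided 0.05, power 0.80, dropout 20%, N = 104 at 1:1, visits at baseline and weeks 4, 8 and 12. With 20% dropout, 104 × 0.8 / 2 = 41.6, taken as n = 42 per arm.

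**The plan's own figure.** A two-sample t test with d = 0.57 needs 50 per arm, 100 in total, or 100 / 0.8 = 125 with dropout. The stated 104 is not reproduced. That is a separate matter; here 0.57 serves only as a common yardstick.

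**Assumptions.** SD 1 at each visit, compound symmetry with correlation ρ = 0.3, 0.5 or 0.7, complete data on 42 per arm. Differences between arms at the four visits are 0, 0.19, 0.38, 0.57 (linear) or 0, 0.57, 0.57, 0.57 (immediate).

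**Dilution of the group main effect.** Mean difference: linear (0 + 0.19 + 0.38 + 0.57) / 4 = 0.285, which is 50% of 0.57; immediate 3 × 0.57 / 4 = 0.4275, which is 75%.

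**Noncentrality parameters.**
- Interaction: λ = (n/2) S / (1 − ρ), where S is the sum of squared deviations of the visit differences from their mean; df 3 and 246. S = 0.1805 (linear) or 0.2437 (immediate). At ρ = 0.5, linear: 21 × 0.1805 / 0.5 = 7.58.
- Group: λ = (n/2) × (mean difference)² / ((1 + 3ρ)/4); df 1 and 82. At ρ = 0.5, linear: 21 × 0.0812 / 0.625 = 2.73.
- Week-12 ANCOVA: λ = (n/2) × 0.57² / (1 − ρ²); df 1 and 81. At ρ = 0.5: 21 × 0.3249 / 0.75 = 9.10.

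| Effect | ρ | Interaction | Group main effect | Week-12 ANCOVA |
|---|---|---|---|---|
| Linear | 0.3 | 46.7% | 46.5% | 77.2% |
| Linear | 0.5 | 62.0% | 37.2% | 84.6% |
| Linear | 0.7 | 85.4% | 31.1% | 95.1% |
| Immediate | 0.3 | 60.3% | 80.2% | 77.2% |
| Immediate | 0.5 | 76.4% | 68.8% | 84.6% |
| Immediate | 0.7 | 94.5% | 59.5% | 95.1% |

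Simulation agrees within about 2 points: interaction 47/62/85% and ANCOVA 76/83/95% (linear), 60/78/95% and 77/84/94% (immediate). With all 52 per arm and a linear effect, the interaction has 56/72/93% and ANCOVA about 85/91/98%.

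**No treatment effect, both arms improving.** Let both arms rise by 0, 0.2, 0.4, 0.6 SD. Then S = 0.20 and λ = 84 × 0.20 / (1 − ρ). At ρ = 0.5 this is 33.6 and the time effect is significant in 99.9% of trials; at ρ = 0.3 it is 24.0, giving 99.0%. In simulation the interaction stays at about 5%.

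**No effect and no trend.** At least one of the three F tests is significant in 13.9% of simulated trials, close to 1 − 0.95³ = 14.3%.

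**The case against.** The strongest reply is that the plan already contains a correct test. In a randomised two-arm trial the group-by-time interaction is a valid test of differential change and keeps its 5% error rate when both arms improve. That stands, so a reader who infers that the plan tests only the wrong effects goes too far. The weakness is that this test is not singled out.

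The text also ties significant effects to post hoc comparisons, not to efficacy claims. That stands too. The near-100% rate for the time effect is a rate of opening further testing; it would be a false-positive efficacy rate only if the effect were misread. The 0.6 SD improvement is an assumption, and selection at entry supports regression to the mean for CAIT only.

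A reader might also infer that a real week-12 effect will probably be missed. Requiring a significant interaction plus a week-12 comparison at 0.05/4 gives about 39 to 41% power at ρ = 0.5 with a linear effect. But no Bonferroni family is stated. At 0.05 for week 12 the figure is 52%, and it rises with an earlier effect or higher correlation.

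Finally, ANCOVA does not always win. With an immediate effect and ρ = 0.3, the group main effect is slightly ahead (80% against 77%). If correlation decays between visits (AR(1)), an early effect can favour the planned tests by more. At 41 per arm, the interaction has 91% against 84% at ρ = 0.8, and the group main effect 87% against 72% at ρ = 0.3. The power argument is therefore conditional. The argument about the missing deciding test does not depend on it.

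**Conclusion.** The point holds in limited form. The plan lets time and group main effects, as well as the interaction, open post hoc testing and does not say which result answers the efficacy question. The time effect carries no information about treatment, and the group main effect is diluted to 50 to 75% of the week-12 difference if baseline is a level of time.

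Against a baseline-adjusted week-12 comparison under compound symmetry, the interaction loses about 30, 23 and 10 points at ρ = 0.3, 0.5 and 0.7 if the effect builds linearly. If the effect is immediate it loses about 17, 8 and 1. These figures rest on d = 0.57, 42 per arm and complete data; the documents give no correlation or trajectory, so they are a range and not a forecast. The documents do not support saying that the planned analysis is invalid, that main effects are meant as efficacy claims, or that a true effect will probably be missed.

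**What to change.** In section {20a}, for each primary outcome, name as the deciding test the between-group difference at week 12 adjusted for that outcome's baseline value, two-sided at 0.05, with a 95% CI. Use either ANCOVA or a mixed model for weeks 4, 8 and 12 with group, visit, group-by-visit and baseline (with baseline-by-visit). Make the weeks 4 and 8 differences secondary. Report time main effects and within-group changes descriptively, and state that they neither open nor support an efficacy conclusion. If the authors prefer to keep the repeated ANOVA, the minimum change is to name the interaction as the deciding test and drop the main effects as triggers.

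This does not settle how the several primary outcomes are to be handled together, which needs its own statement.

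The cost is small: baseline is already collected and no visit or procedure changes. The trial status section says the trial is underway, so the change is an analysis amendment to be notified as section {25} provides, and best made before unblinded data are seen. Some power may be given up if the effect is early: against the interaction at high correlation, or against the group main effect at low correlation.

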### Interim analyses {21b}

Not applicable. Interim testing will not be conducted in this study.

### Methods for additional analyses (e.g., subgroup analyses) {20b}

Not applicable. No subgroup will be established in this study.

### Methods in analysis to handle protocol non-adherence and any statistical methods to handle missing data {20c}

If any participant withdraws from the trial, the last observation-carried forward method and multiple imputation method will be respectively conducted to adjust for the missing data.

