**Fig. 2 Fig2:**
[figure not shown]
The core program consisting of nine forms of STCEP

Form A: part the wild horse’s mane (stepping diagonally forward: left and right)

Form B: step back up and whirl arms (stepping backward: left and right)

Form C: brush knee and twist step (stepping forward: left and right)

Form D: cloud hands. Form E: single whip (stepping sideways: left and right)

Form F: pushing down and single on one leg (stepping diagonally forward: left and right)

Form G: heel kick (in situ: left and right)

Form H: grasp the bird’s tail (stepping sideways: left and right)

Form I: cross-hand (stepping sideways: left and right)

The exercise routine emphasizes the practice of ankle joint movements with more repetitions in multiple directions, which may help improve the neuromuscular function of ankle joints in patients with FAI. These movements are usually maintained in a semi-squat and one-leg stance, controlling the displacement of the center of gravity in three anatomical planes. The coordination of all body parts plays a vital role in maintaining precise motor control while keeping balance. Any simple action in the traditional 24-style Tai Chi program that involves fewer foot-ankle movements is removed. Afterward, the rest of the movements are rearranged according to the suggestions of Tai Chi experts. The exercise program will be specially designed to promote the neuromuscular control of patients with FAI.

The participants in the STCEP group will receive 12 weeks of the STCEP training, three sessions per week, and 60 min per session. Each session will include 5 min warm-up exercises, 50 min practice, and 5 min cool-down exercises. Every training session will be led and monitored by a professional Tai Chi instructor, who will carefully guide the exercise and correct inappropriate movements.

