### Criteria for discontinuing or modifying allocated interventions {11b}

Study patients will be allowed or asked to withdraw from the study if:
Participants decide to withdrawParticipants develop serious diseases, such as heart disease or strokeParticipants have an adverse reaction related to the STCEP programParticipants missed more than three training sessions in the 12-week program

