### Outcomes {12}

Demographic information, primary outcomes, and secondary outcomes will be collected. Demographic information will be collected at baseline (1–2 weeks before randomization) via a questionnaire. Primary and secondary outcomes will be measured at baseline, 4th, 8th, and 12th weeks of training. The schedule of study outcome assessments is outlined in Fig. 3.

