#### Primary outcome assessments

Cumberland Ankle Instability ToolThe CAIT is a valid and reliable evaluative instrument used to assess self-rated ankle instability [17]. It consists of eight items for ankle instability in sports/daily activities and one item for ankle pain. The scores from the nine items are added to obtain a final score. The final score ranges from 0 (worst) to 30 (best).Biomechanical analysis during mSEBTmSEBT is a test that has been commonly utilized as a modified version of the SEBT to dynamic balance in clinics for the CAI groups [18]. In this test, participants stand on a single leg on the center of a force platform with hands on the waist as the starting position for the test. They maintain a single-leg stance and slowly reach the contralateral leg as far as they could along the anterior, posteromedial, or posterolateral directions. They tap their toes without shifting the body weight to the reaching limb and then return to the starting position while maintaining their single-leg stance balance for about 10 s. They perform three trials on each foot. In this study, the mean distance from the three trials will be used for analysis.Kinetic data will be simultaneously collected using two force plates (AMTI) with a sampling frequency of 1000 Hz in combination with the mEMG of the leg muscles for the mSEBT test. Rectangular electrodes with parallel bar electrodes are placed bilaterally over the muscle belly of the rectus femoris, biceps femoris, tibialis anterior, and peroneus longus [19].Biomechanical analysis during the single-leg drop landingA 40-cm-high box is placed 5 cm posterior to the force plate [20]. Before the test trial, the subjects are provided three trials to practice the maneuver. The participants are first asked to stand on the box with hands on the waist. The examiner gives the verbal command of “Ready,” and the participants stick out the tested leg and keep balance. As soon as hearing the command of “Start,” the participants jump straight down from the box, land on the tested leg at the center of the force plate, and stabilize as quickly as possible. They keep the single-leg stance balance for at least 5 s. Between trials, a 30-s rest will be provided. A trial will be discarded and repeated if the participants lose balance after landing or use their hands/feet are used to restore balance.Lower extremity kinematic data will be obtained using a three-dimensional motion capture system by 12 infrared cameras at 100 Hz (Vicon, Oxford, UK) and in combination with ground reaction force data, which will be measured by two force plates (AMTI) with a sampling frequency of 1000 Hz and in combination with the sEMG of the leg muscles for the landing task. The markers will be placed bilaterally on the first metatarsal head, first and fifth metatarsal phalangeal joints, medial and lateral malleoli, posterior calcaneus, medial and lateral femoral epicondyles, greater trochanters, anterior iliac spine, iliac crest, posterior iliac spine, and the fourth lumbar vertebra.

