### Adverse event reporting and harms {22}

The trial will not use investigational medicinal products, and the researchers have already obtained the practicing certificate of a rehabilitation therapist with abundant clinical experience. The participant will be monitored and documented during the study intervention. Any adverse events (defined as any functional impairment caused by the intervention, such as ankle sprain, ankle pain, and pallor) will be recorded. If serious adverse events occur, the participants will immediately discontinue the intervention and receive appropriate treatments. Incidents will be reported to the Ethics Committee of Shandong Sport University.

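### Missing outcomes are handled only after withdrawal, so the repeated ANOVA would drop participants who stay in the trial but lack a value at one visit

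*Protocol article*

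**What the plan says.** The section on non-adherence and missing data {20c} is a single sentence, which begins: "If any participant withdraws from the trial, the last observation-carried forward method and multiple imputation method will be respectively conducted". Withdrawal is the only trigger it names.

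The statistical methods section {20a} fixes the analysis: "Two-way repeated ANOVA will be used to determine the main effects of groups, intervention time, and interaction on the measurements". The outcomes section {12} sets four time points: "Primary and secondary outcomes will be measured at baseline, 4th, 8th, and 12th weeks of training".

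Two other sections decide who counts as withdrawn.

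- The discontinuation section {11b} opens "Study patients will be allowed or asked to withdraw from the study if" and lists four grounds: the participant's own decision, serious disease, an adverse reaction related to the STCEP programme, and more than three missed sessions. Only the third names an arm.
- The adverse event section {22} defines events as impairment caused by the intervention, "such as ankle sprain, ankle pain, and pallor". It names no arm. After a serious event it stops the intervention, without saying that the participant leaves the trial.

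**The concern.** Withdrawal and missing data are not the same thing. Several outcomes need an ankle fit for testing on the day: the drop landing from a 40 cm box, the mSEBT, the leaps of the DLBT and isokinetic strength. The background section describes a high rate of recurrent sprain in this population, and the harms section expects sprain and pain. A participant may be unable to do a task at one visit, or may miss the visit, without leaving the trial. For the landing task the protocol says "A trial will be discarded and repeated if the participants lose balance after landing". That covers a failed attempt within a session, not a participant who cannot complete the task at all.

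Two things are at stake. The first is the loss of data already collected: one empty visit removes the participant's other three values for that outcome. The second is selection: the people removed are likely to have the worse ankles, and ankle function is what the trial measures. The set analysed would also change from one outcome to the next.

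This point is about which missing values get any rule. It does not concern the choice between the two imputation methods.

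**Working it through.** **Which cases are covered**

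| Situation | Rule in {20c}? | Result under the ANOVA in {20a} |
|---|---|---|
| Participant withdraws | Yes, LOCF and multiple imputation | Kept, with filled values |
| Stays in, misses a visit | None stated | Row incomplete, dropped |
| Stays in, attends, cannot do a task | None stated | Row incomplete for that outcome, dropped |

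The last column follows from how the classical method works. The protocol does not itself mention deletion.

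**Size of the loss**

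The plan gives no figure to reproduce here. Inputs from the protocol are 104 participants and three follow-up visits. The missing rate p at each follow-up visit is my assumption, with nobody withdrawn.

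If gaps are independent across visits, the share lost is 1 − (1 − p)³:

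- p = 3%: 1 − 0.97³ = 0.087, and 0.087 × 104 ≈ 9 participants
- p = 5%: 1 − 0.95³ = 0.143, and 0.143 × 104 ≈ 15 participants
- p = 7%: 1 − 0.93³ = 0.196, and 0.196 × 104 ≈ 20 participants

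Independence matters, because an injured ankle tends to miss adjacent visits. At the extreme where the same people miss all three visits, the loss is only p: 3%, 5% or 7%, or about 3, 5 or 7 of 104. Real losses would probably lie between the two sets.

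I attach no power figure. The sample size section gives the effect size of 0.57 alongside CAIT data. CAIT is a questionnaire that an injured participant can still complete, so 0.57 is a poor basis for the landing, balance and strength outcomes.

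**Where the arms can differ**

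The STCEP schedule is "12 weeks of the STCEP training, three sessions per week, and 60 min per session", so 12 × 3 = 36 sessions. The control group's weekly schedule is identical. More than three missed means at least 4, and 4/36 = 11%, just over one week of training. A participant in either arm whose ankle problem costs four or more sessions therefore meets a withdrawal criterion and comes under the missing-data rule.

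The arms can be treated differently only for events that cost three sessions or fewer and do not lead the participant to leave by choice. Such an event in the STCEP arm, if judged related to the programme, meets the adverse-reaction criterion. The same event in the control arm meets none. A short flare that overlaps an assessment fits this window.

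**The case against.** The strongest objection is that this is only an omission. Rules for intermittent gaps often sit in a full protocol or SAP, neither of which is shown, and the article never says that incomplete participants are deleted. This stands in part: a fuller document may already cover the case. But the article is not silent. It states a rule, limits that rule to withdrawal, and names an analysis that needs complete rows. Followed as written, those two statements discard observed data.

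The missing rates are assumed and the independence formula is an upper-side figure. Both points stand. Nor do the figures show that the 20% drop-out allowance would be exceeded.

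A reader might go further and infer that the same sprain is imputed in the STCEP arm and deleted in the control arm, so that the treatment effect is biased by a calculable amount. The protocol does not support this, for four reasons:

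- Withdrawal is allowed or asked for, so it is not automatic in the STCEP arm.
- Participants in either arm can leave by choice or meet the attendance criterion.
- A sprain unrelated to the programme does not trigger the STCEP criterion.
- The harms section names no arm.

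Nor does a bias equal to sprain rate times severity follow. It would require withdrawn STCEP participants to keep their injured scores, and those scores are never observed. If their values are instead imputed from uninjured STCEP participants while injured controls are deleted, each arm is represented by its uninjured members, and the expected difference stays at about 0.57. LOCF would give another answer again.

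**Conclusion.** The concern holds in a limited form. As written, the missing-data rule leaves out retained participants with a gap, and the named ANOVA would drop them. Under the assumed 3% to 7% per visit, the loss is about 9% to 20% of participants if gaps are independent, and less if they cluster. That these gaps depend on ankle status is probable, given the tasks and the population, but it is a judgement.

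The difference between arms is a possible route to unequal handling, confined to short events. The protocol does not allow its size or direction to be stated. The gap should be closed before analysis, but it does not show that the trial's result would be wrong.

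**What to change.** Reword {20c} along these lines: all randomised participants are analysed in their assigned arm, and any missing outcome value at week 4, 8 or 12, whatever the reason and whether or not the participant has withdrawn, is handled by the same method in both arms.

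In {20a}, replace the complete-row ANOVA with a linear mixed model that keeps incomplete rows, or retain the ANOVA after multiple imputation that uses all available visits. Either approach uses the participant's observed visits. Neither fully removes the problem if missingness depends on an ankle state that no recorded value reflects.

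The withdrawal grounds in {11b} and the adverse event rules in {22} should be reconciled, so that it is clear to which arm or arms each applies. Which rule to adopt is for the investigators.

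The cost is changed wording and slightly more analysis work. No extra participants or visits are needed.
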